## Abstract

**Background:**

A significant part of neurological rehabilitation focuses on facilitating the learning of motor skills. Training can adopt either (more) explicit or (more) implicit forms of motor learning. Gait is one of the most practiced motor skills within rehabilitation in people after stroke because it is an important criterion for discharge and requirement for functioning at home.

**Objective:**

The aim of this study was to describe the design of a randomized controlled study assessing the effects of implicit motor learning compared with the explicit motor learning in gait rehabilitation of people suffering from stroke.

**Methods:**

The study adopts a randomized, controlled, single-blinded study design. People after stroke will be eligible for participation when they are in the chronic stage of recovery (>6 months after stroke), would like to improve walking performance, have a slow walking speed (<1 m/s), can communicate in Dutch, and complete a 3-stage command. People will be excluded if they cannot walk a minimum of 10 m or have other additional impairments that (severely) influence gait. Participants will receive 9 gait-training sessions over a 3-week period and will be randomly allocated to an implicit or explicit group. Therapists are aware of the intervention they provide, and the assessors are blind to the intervention participants receive. Outcome will be assessed at baseline (T0), directly after the intervention (T1), and after 1 month (T2). The primary outcome parameter is walking velocity. Walking performance will be assessed with the 10-meter walking test, Dynamic Gait Index, and while performing a secondary task (dual task). Self-reported measures are the Movement Specific Reinvestment Scale, verbal protocol, Stroke and Aphasia Quality of Life Scale, and the Global Perceived Effect scale. A process evaluation will take place to identify how the therapy was perceived and identify factors that may have influenced the effectiveness of the intervention. Repeated measures analyses will be conducted to determine significant and clinical relevant differences between groups and over time.

**Results:**

Data collection is currently ongoing and results are expected in 2019.

**Conclusions:**

The relevance of the study as well as the advantages and disadvantages of several aspects of the chosen design are discussed, for example, the personalized approach and choice of measurements.

**Trial Registration:**

Netherlands Trial Register NTR6272; http://www.trialregister.nl/trialreg/admin/rctview.asp?TC=6272 (Archived by WebCite http://www.webcitation.org/6ytA937m5)

**Registered Report Identifier:**

RR1-10.2196/9595

## Introduction

### Background and Rationale

For most people, walking is a motor skill that generally takes place without too much effort. However, for people who have suffered a stroke, walking is often suddenly impaired, which can lead to major consequences in daily life functioning. People may experience impaired walking patterns with lower walking speeds, which has been associated with lower levels of functional ambulation [1]. Gait training is one of the main components of physiotherapy within stroke rehabilitation because it is an important criterion for discharge and requirement for functioning at home [1,2]. Evidence suggests that even in later (chronic) stages after stroke, people are still able to improve motor performance [3]. Many different techniques and therapies can be used to improve walking performance [4]; the challenge for physiotherapists is to choose and deliver gait training in the most efficient and effective manner. Moreover, preferably, obtained improvements in performance are durable over a longer period and resilient under different circumstances and in dual-task situations, for example, walking and talking. Despite the availability of new training approaches such as the use of robotics [5], virtual reality, for example through exergames [6,7] or body weight support training [8], overground walking [9] still seems one of the most applied gait-training approaches in clinical practice. The current literature and clinical guidelines encourage the use of context- and task-specific treatment approaches, an example of which is overground walking [4,10].

To apply overground gait training, physiotherapists are encouraged to use general motor learning principles [10]. Within the context of motor learning, a broad distinction between implicit and explicit motor learning has been described [11,12]. Explicit motor learning can be defined as learning generated by verbal knowledge of movement performance; it involves cognitive stages within the learning process and is dependent on working memory involvement [13]. The definition indicates that the learner is aware of all the underlying facts and rules of the to-be-learned motor skill during the process of learning. In practice, verbal explicit instructions are frequently used, and often these instructions encourage patients to be aware of their own body movements [14]. For example, in gait training, therapists tell patients to think about their performance, for example, “Move your hips to the left and straighten your knee before stepping” [14].

In contrast to explicit learning, implicit motor learning progresses with no or minimal increase in the verbal knowledge of movement performance (eg, facts and rules) and without awareness [13]. Learning is suggested to take place more automatically and in a less conscious manner. The learner is aware of the process of learning but cannot recall the underlying facts and rules of the motor skill. Gait training could be facilitated more implicitly, for example, when a physiotherapist would gradually constrain or change the environment, for example, when letting the person walk over different surfaces. In this situation, verbal instructions are not needed, but the environment facilitates the motor skill (walking). An observational study demonstrated that often multiple learning strategies are being used within one training session [15]. These different learning strategies may represent an implicit-explicit continuum on which some promote more implicit and others more explicit forms of learning [11]. Looking at the current practice, therapists seem to have a preference for learning approaches that are related to explicit learning in which often high numbers of verbal explicit instructions are used [14].

Various advantages of implicit motor learning over explicit motor learning have been reported in literature [12]. Studies have demonstrated that individuals who learned motor skills implicitly perform the motor skill better under pressure, perform better in dual-task situations, and perform better over time compared with their explicit counterparts [12,16,17]. Although these studies have primarily been conducted within the healthy population, implicit learning may also be advantageous for the patient population [18,19]. For example, implicit motor learning may be of extra benefit to those with cognitive deficits [20]. Reduced cognitive function is frequently seen in people after stroke [21] and it often hampers the process of motor learning. The degree by which these cognitive functions are being evoked can be influenced by the choice of learning approaches [20]. An interesting feature of implicit motor learning is the assumption that it is less reliant on working memory resources, that is, it involves less cognitive functions, compared with explicit motor learning [19]. It is, therefore, intriguing to explore the effects of implicit motor learning within the stroke population.

Although from a theoretical perspective, the features of implicit motor learning have been described, its practical application in clinical practice seems more complex. Various learning strategies, for example, dual task, or errorless learning have been shown to promote implicit motor learning [17,22]. One learning approach that may also be placed more on the implicit side of the implicit-explicit continuum is analogy learning. In analogy learning, the learner is provided with one single analogy or metaphor that strives to combine all the relevant rules of the to-be-learned motor skill. Early studies on analogy learning took place within a sporting context, for example, to learn specific skill techniques in table tennis or basketball [23,24]. A good example in this regard was presented by Lam and colleagues [23]. They used the analogy instruction “Shoot as if you are trying to put cookies into a cookie jar on a high shelf” to teach basketball players to impart backspin on the basketball. At present, there seems an increased interest of its application within different contexts. Analogy studies have been performed with older people [25] in the context of speech therapy [26] and within neurological populations [27,28]. For example, the analogy “imagine as if you are walking over a frozen lake” has been used in gait rehabilitation to facilitate lifting and placing the foot while walking [28]. With regard to gait rehabilitation, small pilot studies have reported that analogies can be used in a feasible manner to facilitate walking performance [27,28]. It has been reported that the analogy should lead to the desired biomechanical movement and that preferably the analogy should contain a meaningful component to the participant [28,29]. In addition to feasibility, trends toward improved walking performance have been observed following analogy interventions, which demonstrates the potential of analogy learning in clinical practice [27,28]. However, to further establish the effectiveness of analogy learning in clinical gait rehabilitation, larger sample sizes and research designs using a control condition are required.

This study describes the design for a randomized controlled study to assess the effects of implicit motor learning compared with explicit motor learning on walking speed in people suffering from stroke. The concept of analogy learning is used to structure the gait-training sessions within the implicit condition, whereas explicit motor learning is promoted by using extensive verbal instructions and feedback. A process evaluation is embedded to investigate feasibility and fidelity of the applied interventions.

### Research Question

The following research question was established to examine the effects of implicit and explicit motor learning in gait rehabilitation of people after stroke: Is a 3-week implicit motor learning walking intervention (analogies) more effective compared with a 3-week explicit motor learning walking intervention (verbal detailed instructions) delivered at home with regard to walking speed in people suffering from stroke?

## Methods

### Study Design

The study adopts a randomized, controlled, single-blinded study design in people suffering from stroke in the chronic stage of recovery. The study has been approved by the local ethics committee METC-Z in Heerlen, the Netherlands (NL number: NL.60338.096.16, Ethics nr: 17-T-06). After baseline measures, eligible participants will be randomized to the implicit or explicit condition (T0). Outcome assessments will take place directly after the intervention (T1) and again one month later (T2).

### Involvement of Client Representatives

Throughout the design and planning of the study, 3 patient representatives were involved in every step of the decision-making process regarding the design and execution of the study. In several consensus meetings, they represented the patient’s perspective, particularly with regard to the feasibility aspects of the study design. They were also involved in customizing participant information letters and promotion material for the study.

### Population

The study population consists of people who had a stroke and who are living at home. People will be recruited via local private practices, rehabilitation institutes, and a local health-related newspaper. Participants will be included if they had a stroke and want to improve their gait performance. To minimize the chance that improvements occur as a result of spontaneous recovery, only participants who are in the chronic stage of recovery (>6 months after stroke) will be included in the study. To prevent a ceiling effect, people with a low self-selected walking speed (<1.0 m/s) will be invited to participate. Finally, all people should be able to communicate in Dutch and complete a 3-stage command. People are excluded if they are unable to walk a minimum distance of 10 m; have a functional ambulation category score <3; have additional impairments not related to stroke, which influence their gait pattern, for example, severe osteoarthritis or amputation of the lower limb; have additional neurological impairments, for example, Parkinson disease that (severely) influence their walking performance.

### Sample Size

The sample size calculation is based on a randomized controlled trial with equal group sizes and “walking speed” (10-meter walking test, 10MWT) as a primary outcome measure [30]. The power is set at beta=.80, the significance level at alpha=.05, and a standard deviation of 0.23 m/s [31]. To demonstrate a significant change in walking speed, the minimal clinically important difference (MCID) is used and set at a minimum change of 0.16 m/s [32,33]. The calculations resulted in a minimum group size of 33 participants per group. Taking into account that 20% (7/33) of participants may be lost during (dropout) and after the intervention (loss to follow-up), this study aims to recruit 40 participants per group.

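### The 20% loss allowance is added to the 33 completers needed, so 40 recruits per group leave 32, one short of the stated minimum; the effect on power is small

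*Protocol article*

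**What the plan says.** Everything needed is in one paragraph, the Sample Size section of the protocol article. The inputs are "the significance level at alpha=.05", power of 80% (printed as "The power is set at beta=.80"), "a standard deviation of 0.23 m/s", and a difference "set at a minimum change of 0.16 m/s", for "a randomized controlled trial with equal group sizes". The result is given as follows: "The calculations resulted in a minimum group size of 33 participants per group". The section then allows for attrition, stating that "20% (7/33) of participants may be lost during (dropout) and after the intervention (loss to follow-up"), and concludes that "this study aims to recruit 40 participants per group".

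**The concern.** A loss rate describes what happens to the people who enter the trial, so it applies to the number recruited. The fraction printed beside the 20% has the 33 completers as its denominator, which suggests that the allowance was computed on the wrong base. If so, the recruitment target does not protect the minimum that the same paragraph sets. Two things are at stake. One is whether the three stated figures (33 needed, 20% lost, 40 recruited) agree. The other is how much power is lost if attrition is in fact 20%. Readers of the results will also judge actual retention against the stated 20%, so the figure should be the loss that the design can absorb.

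**Working it through.** **Inputs** (all from the Sample Size section): difference δ = 0.16 m/s, SD σ = 0.23 m/s, α = .05, power 0.80, equal groups, loss 20% (printed as 7/33), recruitment 40 per group. The section does not say whether the test is one- or two-sided. Two-sided is assumed because it reproduces the plan's 33, while a one-sided test gives 26 to 27 per group.

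**1. Reproduce the 33.** Normal formula for two independent means:

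n per group = 2 × (z₀.₉₇₅ + z₀.₈₀)² × (σ/δ)² = 2 × (1.960 + 0.842)² × (0.23/0.16)² = 32.44 (from unrounded quantiles), so 33.

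This matches the plan. The t-test version gives 33.4, so 34, a trivial difference.

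**2. Reproduce the 40.** 20% of 33 = 6.6, rounded to 7, and 33 + 7 = 40. Equivalently, 33 × 1.20 = 39.6, so 40. The target is therefore the completers needed plus 20% of the completers.

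**3. Apply the loss to those recruited.**
- Remaining after 20% loss from 40: 40 × 0.80 = 32, one below 33.
- Recruits needed for 33 completers: 33/0.80 = 41.25, so 42 per group (84 in total against 80).
- From the unrounded requirement: 32.44/0.80 = 40.55, so 41 per group.

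The target is thus 1 to 2 per group low, depending on where one rounds.

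**4. Check the printed fraction.** 7/33 = 21.2%, not 20%. Seven losses among 40 recruits is 7/40 = 17.5%, which leaves exactly 33.

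**5. Effect on power.** By the normal formula, power = Φ(δ/(σ√(2/n)) − 1.960).
- n = 32: (0.16/0.23) × √16 = 2.783; 2.783 − 1.960 = 0.823; Φ = 0.795.
- n = 33: (0.16/0.23) × √16.5 = 2.826; 2.826 − 1.960 = 0.866; Φ = 0.807.

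| Evaluable per group | Normal formula | t-test |
|---|---|---|
| 33 | 80.7% | 79.5% |
| 32 | 79.5% | 78.2% |

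Losing that one participant per group costs 1.2 points by the normal formula (80.7 − 79.5) and 1.3 by the t-test (79.5 − 78.2). Against the 80% target, the shortfall at 32 is 0.5 points (normal) or 1.8 points (t-test). Of the latter, 0.5 points are already there at 33 and have nothing to do with attrition.

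**The case against.** The best defence is that the section also prints the loss as a count. If seven people per group are lost, 40 − 7 = 33 and the target is met, so only the percentage is mislabelled. The 20% is also a forecast, and nothing in the document separates it from 17.5%. This explains how the authors arrived at 40 and supports keeping it. It does not rescue the sentence: the stated rate is 20% of participants, 7/33 is not 20%, and 20% of 40 recruits is eight people, not seven.

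It is also fair to say that 42 is the upper end of the correction, since the unrounded requirement leads to 41, and that 79.5% power on the plan's own formula is a negligible departure from 80%. Both points stand and set the size of the finding.

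The power figures describe a simple two-group comparison, whereas the Data Analyses section plans a repeated-measures analysis over three time points. Power under that analysis could be higher or lower. The figures above measure the slip on the basis that reproduces the plan's 33; they do not predict the power of the final analysis.

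**Conclusion.** The allowance is wrong as written: 33 needed, 20% lost and 40 recruited are inconsistent, because a 20% loss leaves 32 per group. The discrepancy is one evaluable participant per group, or 1 to 2 recruits per group, and the severity is minor. The size in power rests on a two-sided .05 unadjusted comparison with SD 0.23 m/s and difference 0.16 m/s: 79.5% instead of 80.7% (normal), or 78.2% instead of 79.5% (t-test).

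Three stronger readings are tempting but not supported:
- A reader might infer that the trial is materially underpowered. A change of just over one percentage point does not show that, and the planned analysis is not the one that these figures describe.
- A reader might infer that the shortfall grows because the Data Analyses section processes only participants with at least seven sessions. The same section also plans an intention-to-treat analysis, and the 20% already includes dropout during the intervention. The document therefore does not show how many further participants, if any, would be removed.
- A reader might infer, in the other direction, that baseline adjustment makes up the loss. No correlation between baseline and follow-up is given, and the section does not say whether 0.23 m/s is the SD of speed or of change, so this cannot be claimed.

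**What to change.** Keep 40 per group and replace the attrition sentence with wording such as: *40 per group allows for 17.5% loss (7/40), leaving 33 evaluable per group; with 20% loss, 32 per group remain and power is about 78–79.5% for an unadjusted two-sided comparison at .05.*

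This corrects both the base and the fraction. The cost is one sentence and a slightly less favourable stated tolerance for loss. It needs no extra participants and no change to the design. Keeping the 20% figure with 33 as the minimum would instead mean recruiting 42 per group, four more in total; the size of the power effect does not call for that.

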### Randomization, Blinding, and Treatment Allocation

#### Randomization Procedure

The allocation of participants to the experimental or the control condition will occur based on a computerized randomization program. Block randomization was calculated in block sizes of fours and sixes. The randomization procedure and the randomization scheme will only be available to an independent researcher who will not be involved in the delivery of the interventions or the performance of the measurements.

#### Blinding

The trained assessors are blind for treatment allocation. The therapists are aware of the treatment condition as they provide the explicit or implicit motor learning condition. The participants will probably also be aware of the treatment they receive; however, they will not be specifically told. The participants will be asked at each assessment not to reveal the details of treatment they received to the blinded assessor.

#### Training of Therapists and Treatment of Participants

An intervention guideline is developed that outlines how the treatments (implicit and explicit conditions) should be delivered. The main aim of the intervention is to improve the quality of walking performance in people after stroke. The basic principle of the intervention guideline is based on the definitions of implicit and explicit motor learning by Kleynen et al [11]. For the purpose of this study, we strive to create the largest contrast between the conditions as possible. The main characteristics and differences in instructions, and feedback of the practice between interventions are described in Figure 1. Both conditions will always be applied to an extent that is feasible for the participant, and training will therefore always be tailored to the participant’s abilities within the given boundaries of the condition. Similar situations will be adopted in both conditions with regard to the “organization” of the training, for example, use variation in the (analogy) instructions and practice of the motor skill.

The chosen intervention period was based on a preliminary study of Kleynen et al [28] that demonstrated that 3 weeks was a feasible period to develop and practice analogies with people after stroke. All participants will receive 9 training sessions in a 3-week intervention period, that is, 3 training sessions per week (Figure 2). Each training session takes place at the home of the participants and lasts for 30 min. Participants were asked to use the instructions in daily life (unguided therapy) and after the 3-week intervention period. To standardize the training content as much as possible, the therapists involved in the study will be trained before the start of the study. During 5 standardization training sessions, the intervention guideline will be discussed, explicated, and the therapists will be trained with the help of example cases. During the trial, therapists will attend 3 evaluation sessions to discuss the progress of the study and possible cases or difficulties they may experience during the intervention.

**Figure 1 figure1:**
[figure not shown]
Characteristics of the interventions.

**Figure 2 figure2:**
[figure not shown]
Overview of the gait training sessions.

### Implicit Condition

Within the implicit condition, the concept of analogy learning is the leading approach as it has shown to adopt characteristics of implicit motor learning [24,27,28] and provides therapists with a practical and feasible guideline to organize gait training. To choose and develop appropriate analogies, the same procedure as used by Kleynen et al is followed [28]. A booklet with examples of possible analogies will be available for the therapists and patients as a source of inspiration. Preferably, analogies are developed based on the participants’ experiences and background to promote the personalized and meaningful aspects of analogy learning [28]. All analogy instructions used in the trial will be documented. In addition to analogy learning, the therapists are allowed to use elements based on the characteristics of implicit motor learning as reported under the implicit column in Figure 1.

